## Abstract

**Background:**

An arteriovenous fistula is the optimal form of vascular access in patients with end-stage renal failure requiring haemodialysis. Unfortunately, approximately one-third of fistulae fail at an early stage. Different anaesthetic techniques can influence factors associated with fistula success, such as intraoperative blood flow and venous diameter. A regional anaesthetic brachial plexus block results in vasodilatation and improved short- and long-term fistula flow compared to the infiltration of local anaesthetic alone. This, however, has not yet been shown in a large trial to influence long-term fistula patency, the ultimate clinical measure of success.

The aim of this study is to compare whether a regional anaesthetic block, compared to local anaesthetic infiltration, can improve long-term fistula patency.

**Methods:**

This study is an observer-blinded, randomised controlled trial. Patients scheduled to undergo creation of either brachial or radial arteriovenous fistulae will receive a study information sheet, and consent will be obtained in keeping with the Declaration of Helsinki. Patients will be randomised to receive either: (i) an ultrasound guided brachial plexus block using lignocaine with adrenaline and levobupivicaine, or (ii) local anaesthetic infiltration with lignocaine and levobupivicaine.

A total of 126 patients will be recruited. The primary outcome is fistula primary patency at three months. Secondary outcomes include primary patency at 1 and 12 months, secondary patency and fistula flow at 1, 3 and 12 months, flow on first haemodialysis, procedural pain, patient satisfaction, change in cephalic vein diameter pre- and post-anaesthetic, change in radial or brachial artery flow pre- and post-anaesthetic, alteration of the surgical plan after anaesthesia as guided by vascular mapping with ultrasound, and fistula infection requiring antibiotics.

**Conclusions:**

No large randomised controlled trial has examined the influence of brachial plexus block compared with local anaesthetic infiltration on the long-term patency of arteriovenous fistulae. If the performance of brachial plexus block increases fistulae patency, this will have significant clinical and financial benefits as the number of patients able to commence haemodialysis when planned should increase, and the number of “redo” or revision procedures should be reduced.

**Trial registration:**

This study has been approved by the West of Scotland Research Ethics Committee 5 (reference no. 12/WS/0199) and is registered with the ClinicalTrials.gov database (reference no. NCT01706354).

## Background

When chronic kidney disease (CKD) progresses to irreversible end stage renal failure, renal replacement therapy (RRT) is necessary for survival [1]. Haemodialysis (HD) is the commonest form of RRT. Good quality, stable vascular access is a major factor in determining survival in this group of CKD patients, and surgical creation of an arteriovenous fistula (AVF) is recommended as the optimal technique [2,3]. Unfortunately, approximately one-third of arteriovenous fistulae fail at an early stage [4]. This failure rate is influenced by both the pre-operative arterial and venous diameters and post-operative flow through the AVF, as well as a number of other patient and surgical factors [5,6]. Some anaesthetic techniques can directly influence venous diameter as well as intra- and post-operative blood flow [5], but there is no conclusive evidence as yet that any particular anaesthetic technique can significantly influence long term surgical outcome.

General anaesthesia, regional anaesthesia and local anaesthetic (LA) infiltration are all acceptable anaesthetic techniques for AVF creation. Regional anaesthesia, such as a brachial plexus block (BPB), involves injection of LA around nerves to specifically ‘block’ the motor and sensory nerves that supply the operative site, avoiding the need for general anaesthesia. Whilst general anaesthesia increases intra-operative vasodilatation, CKD patients are known to be at increased risk of peri- and post-operative complications [7,8]. Many of these complications can be avoided if regional or local anaesthesia are employed. Only regional anaesthesia, however, produces an associated sympathetic nerve block which results in an increased intraoperative venous diameter and vessel flow, both intra-operatively and, for several hours, post-operatively [9,10]. Maintenance of adequate blood flow through the fistula post-operatively can help prevent thrombosis and fistula failure and is important in fistula maturation [10]. Furthermore, arterial and venous spasm reduces flow and is more common with local infiltration than regional (or general) anaesthesia [11]. Several non-randomised trials have already demonstrated that, compared to local infiltration, a BPB results in lower immediate AVF failure rates [6,12] and also an improved surgical ability to identify the optimal graft site [13]. The effects, however, of these short-term benefits of regional anaesthesia on long-term AVF survival (patency) remain uncertain. To date there has been no large-scale randomised clinical trial examining this question. Recently it has been demonstrated that a BPB compared to LA alone significantly increased flow through the fistula up until eight weeks after surgery, but this did not translate into any difference in fistula patency [14]. Increased flow is important, but ultimately it is the patency of the AVF that is the major determinant of success. This trial was underpowered and the authors’ final conclusion was that larger scale clinical trials were required.

Anaesthetic technique, therefore, has the potential to modify a number of factors which may influence fistula success. We wish to investigate whether anaesthetic technique can influence fistula patency. Given the higher risks of general anaesthesia in these patients, we wish to compare BPB and LA techniques in an adequately powered trial. We hypothesise that the regional anaesthetic technique of an ultrasound guided BPB will, as a result of improved vasodilation and blood flow at the time of and shortly after surgery, increase the AVF patency rate at three months compared to those undergoing the procedure with LA infiltration. If this is the case, the number of patients able to commence HD when planned should be increased and the number of “redo” procedures should be reduced. This has clear financial implications as well as reducing inconvenience for patients.

## Methods

### Overview

This is a single centre, observer-blinded, randomised controlled trial. This study has been approved by the West of Scotland Research Ethics Committee 5 (reference no. 12/WS/0199) and is registered with the ClinicalTrials.gov database (reference no. NCT01706354). This study will be performed in keeping with the requirements of the Declaration of Helsinki.

### Hypothesis

The creation of arteriovenous fistulae under ultrasound guided brachial plexus block anaesthesia will result in an increased primary patency rate at three months compared to the use of local anaesthetic infiltration.

### Objectives and outcome measures

This study aims to compare local anaesthetic infiltration to a BPB anaesthetic technique for the surgical creation of an AVF, assessing in particular whether an increase in flow at the time of surgery with a BPB alters long-term outcome. The primary outcome measure is AVF primary patency at three months. Primary patency is defined as the unequivocal clinical presence of a thrill or audible bruit indicating flow through the fistula, in a fistula which has not required intervention to maintain or re-establish flow for whatever reason. Secondary outcomes include immediate post-operative patency (within one hour of termination of the procedure), primary patency at one month and one year, primary functional patency at three months and one year (that is, primary patency as described previously but which is also able to deliver flow greater than 350 ml/minutes without recirculation for the duration of haemodialysis), secondary patency at one year (that is, patency maintained by other therapeutic interventions, for example, interventional radiology), flow rates through AVF at one month, three months and one year, flow rates of the radial/brachial artery at one month, three months and one year measured by ultrasound, flow obtained at first HD, flow on HD after one year, change in cephalic vein diameter pre-/post-anaesthetic, change in radial or brachial artery flow pre-/post-anaesthetic, alteration of the surgical plan after anaesthetic and then venous/arterial mapping with ultrasound, AVF infection requiring antibiotics, pain during the procedure, pain one hour post-operatively, patient satisfaction, BPB success, complications including the requirement for conversion to general anaesthesia, the requirement for additional sedation or analgesics peri-operatively, post-operative paraesthesia or weakness suggestive of nerve damage, pneumothorax and time to perform the procedure.

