### Postoperative management

After surgery, patients will be taken to the recovery room and monitored according to standard hospital policy. Patient satisfaction and pain during the procedure will be assessed at this point. Patients will be discharged if they meet day surgery criteria as per hospital policy.

At a time period of one month, three months and one year, a blinded observer will examine AVF clinical patency by palpating for a thrill and auscultating for a bruit. At all these time points patients will be attending routine follow-up clinics or have commenced haemodialysis. Lack of both a thrill and a bruit will result in the fistula being defined as not patent. At the same time, brachial artery volume flow will be measured (as a surrogate for AVF flow) by a blinded observer using Doppler ultrasound as described previously. An average of three measurements will again be made in order to reduce both intra and inter-observer variation. Measurement of brachial artery flow is more reproducible than AVF flows and less prone to intraobserver variability [22]. The probe will be positioned at a distance of 2 to 5 cm cranial to the arterio-venous anastamosis. The point of measurement will be recorded and measurements at three months and one year made at the same position. A minimum of six weeks after AVF creation will be allowed to elapse before the first venipuncture for HD. The flow during the first cannulation of the fistula will be recorded by a blinded observer in the renal patient registry, and also at three months and one year if HD has been commenced at these time points. Finally, at each time point of one and three months and one year it will be noted by a blinded observer if there has been any infection of the AVF requiring antibiotics.

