### Sample size and statistical considerations

Mean AVF failure after formation is reported to lie within the range 25 to 35% [4]. From our own retrospective audit data of patients receiving an ultrasound guided BPB over a two-year period, patients who had received BPB had an AVF survival rate of 93% compared with 52% in patients who received local anaesthetic infiltration [23]. In order to calculate sample size, we made the following assumptions: type 1 error (α) was set at 0.05 and Type 2 error (β) at 0.8. Therefore, if we assume a standard 65% AVF success rate overall, and propose that success rates with the use of BPB will be around 85%, then 57 patients are required in each group. In order to account for attrition of around 10%, we aim to recruit 126 patients. It should be noted that whilst these audit data were significantly in favour of the BPB, the data were retrospective, with non-standardised endpoints and also suffered from all the standard limitations of a retrospective analysis.

The null hypothesis (H0) for this study is that the use of ultrasound guided brachial plexus block does not reduce AVF primary failure rate when compared with local anaesthetic infiltration.

The study will be performed using both intention to treat and “as treated” analysis. In the intention to treat analysis, data will still be analysed from patients where the block has failed (that is if local anaesthetic supplementation is required), or if the patient was unable to receive randomised treatment for any other reason. In the “as treated” analysis, only data from patients completing randomised treatment will be analysed.

Secondary data analyses will be carried out on all secondary outcomes. These will be compared between groups using *t*-test and Mann–Whitney, or Chi-squared tests as appropriate.

It is anticipated that recruitment for this study will take up to two years to complete if one to two patients are enrolled each week. Data collection for each patient will occur during the operative and immediate post-operative period, and at dialysis sessions and post-operative follow-up as directed by the vascular team for one year.

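### Secondary patency, as worded, leaves out fistulae that stay open unaided, so the better arm can score worse; its time points conflict, and haemodialysis flow is not a randomised comparison

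*Protocol article*

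**What the plan says.** Under Objectives and outcome measures, primary patency is a clinically evident thrill or bruit in a fistula that has needed no intervention to keep or restore flow. The same paragraph then lists "secondary patency at one year (that is, patency maintained by other therapeutic interventions, for example, interventional radiology". Nothing there or elsewhere in the article adds that a fistula open without intervention also counts as secondarily patent.

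The abstract gives a different schedule for this outcome: "secondary patency and fistula flow at 1, 3 and 12 months". The Methods list gives secondary patency at one year only.

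Flow at first HD and flow on HD after one year are also secondary outcomes. Under Postoperative management, HD flow is recorded at the first cannulation, which may not take place before six weeks, and "also at three months and one year if HD has been commenced at these time points". Under Sample size and statistical considerations, all secondary outcomes are to be compared between groups by t-test, Mann–Whitney or chi-squared test as appropriate.

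**The concern.** Taken at their word, the two patency definitions are mutually exclusive: one requires no intervention, the other requires patency owed to intervention. Secondary patency then counts rescued fistulae, and that count falls as unaided patency rises. If the trial's hypothesis is true, BPB leaves fewer fistulae in need of rescue and so tends to score lower on an outcome where a higher figure looks like success. A chi-squared test on it could favour LA while more BPB fistulae are open.

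The conflicting time points leave it unclear whether the outcome is assessed once or three times.

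HD flow raises a related but weaker issue. It exists only after two post-randomisation events: the fistula reaching cannulation and the patient starting HD. The first is something the anaesthetic is meant to influence. A between-arm test on the patients who remain is not a comparison of the groups as randomised.

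**Working it through.** **Design rates.** The sample size section assumes 65% success as the standard rate and 85% with BPB, and states "then 57 patients are required in each group". That figure reproduces with 65% taken as the LA rate, power 0.80 (printed as "Type 2 error (β) at 0.8"), a one-sided 5% test, pooled variance and no continuity correction:

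n = [1.645 × √(2 × 0.75 × 0.25) + 0.842 × √(0.65 × 0.35 + 0.85 × 0.15)]² / 0.20² = 56.9, so 57.

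A two-sided 5% test would need 73. Sidedness does not bear on this point; the check only confirms that 65% and 85% are the two arms' rates.

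**Inputs**
- p, the share open without intervention: LA 0.65, BPB 0.85 (protocol, for three months).
- r, the share of the remaining fistulae kept open by intervention: not in the document. Assumed equal in both arms, and varied from 10% to 90%.

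**Formulas**
- Written definition: (1 − p) × r, which falls as p rises.
- Open with or without intervention: p + (1 − p) × r, which rises with p whenever r is below 1.

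| r | Written: LA | Written: BPB | With or without: LA | With or without: BPB |
|---|---|---|---|---|
| 10% | 3.5% | 1.5% | 68.5% | 86.5% |
| 25% | 8.75% | 3.75% | 73.75% | 88.75% |
| 50% | 17.5% | 7.5% | 82.5% | 92.5% |
| 75% | 26.25% | 11.25% | 91.25% | 96.25% |
| 90% | 31.5% | 13.5% | 96.5% | 98.5% |

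For example, at r = 50% the written definition gives LA 0.35 × 0.5 = 17.5% and BPB 0.15 × 0.5 = 7.5%. The other definition gives 0.65 + 0.175 = 82.5% and 0.85 + 0.075 = 92.5%.

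**Unequal rescue rates.** To tie under the written definition, BPB's rescue rate must be 0.35 / 0.15 = 2.33 times LA's. If LA's rescue rate exceeds 0.15 / 0.35 = 43%, BPB cannot tie even if every one of its remaining fistulae is rescued.

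**Chance of a misleading test.** With 57 per arm and r = 50%, the normal-approximation probability of a two-sided significant difference, here favouring LA, is about 36%. It runs from 10% at r = 10% to 64% at r = 90%. Expected counts at r = 50% are about 10 and 4, so these probabilities are rough.

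**HD flow.** The document does not give the share of patients on HD at any time point, so no size can be computed. The point follows from the recording rule: there is no value for a fistula that failed before cannulation or for a patient not yet on HD.

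**The case against.** The wording on secondary patency is a short gloss in a long list of outcomes. No analysis rule says that fistulae open unaided are to be scored as failures, and the full protocol or analysis plan may use a cumulative definition. It is a secondary outcome, and the article says the trial is not powered for all of these. The rescue rates above are assumed. All of that is fair and limits the weight of the point. It does not remove it: the article states the definition, and as stated it gives the wrong ordering at every equal rescue rate. The time-point conflict is largely editorial, but both statements are current text.

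For HD flow, the plan says openly that later values are recorded only once HD has begun. That is an inherent feature of the measure, not a concealed selection. What stands is that the statistics section then sends it to an ordinary between-group test with the other secondary outcomes.

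A reader might extend the argument to two further outcomes. The document does not support either step.

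- **Ultrasound flow.** One might infer that it is compared only among open fistulae. Postoperative management has brachial artery flow measured at the same visits as patency, as a surrogate for fistula flow, with no restriction to open fistulae. It can be measured whether or not the fistula is open. Assigning zero flow to failed fistulae would overwrite values the plan intends to measure.
- **Primary functional patency.** One might infer that it can reverse in the same way. It is primary patency in a fistula "which is also able to deliver flow greater than 350 ml/minutes without recirculation for the duration of haemodialysis", so a failed or revised fistula simply does not qualify. As an illustration, assume 80% functional among the 65% open in either arm and 40% among the further 20% open only with BPB. This gives LA 0.65 × 0.8 = 52% and BPB 0.52 + 0.20 × 0.4 = 60%, with no reversal. How patients not yet on HD are classed is a detail that an analysis plan may hold.

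**Conclusion.** The point holds for secondary patency. As worded, the outcome excludes fistulae open without intervention and favours LA at any equal rescue rate when BPB has the higher unaided patency: by 2 percentage points at r = 10% (3.5 − 1.5) and 18 at r = 90% (31.5 − 13.5). Patency with or without intervention favours BPB by 18 and 2 points at the same rates. The sizes rest on applying the three-month design rates to this outcome, although the Methods place it at one year and give no one-year rates, and on equal rescue in both arms. The direction needs only higher unaided patency with BPB and a rescue rate less than 2.33 times LA's at these design rates.

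The conflict over time points is plain on the face of the article. The HD flow point holds in a weaker form: the data exist only for a subset selected after randomisation, and the size of any distortion cannot be judged from the document. The primary outcome and the sample size are untouched. This should be corrected, but it does not threaten the trial's main result.

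**What to change.** 1. Define secondary patency as the fistula being open at the time point, with or without intervention, among all randomised patients. If the number of fistulae rescued by intervention is of interest, report it separately as a count and not as a success rate.
2. Reconcile the time points for secondary patency between the abstract and the Methods. The text does not show which schedule was intended, so the investigators must say.
3. Report HD flow (at first HD and at one year) descriptively, with denominators by arm: on HD, not on HD, fistula failed. Do not present it as a randomised comparison.

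Items 1 and 2 are wording changes with no added data collection. Item 3 costs the p-value for HD flow, a small loss given that the test would not compare the randomised groups.

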### Study centre

Our centre is a tertiary referral facility for vascular access formation performing around 400 AVF creations per year. The necessary volume of clinical cases, presence of clinical expertise and equipment required for this study is well established in this unit. There is a wealth of experience on the use of ultrasound guidance for regional anaesthetic techniques within the department [15-18].

### Patients and enrolment

Patients scheduled to undergo primary AVF creation will be invited to participate in the study during their pre-assessment clinic visit staffed by the surgeon and the pre-assessment anaesthetic nurse. Inclusion criteria are English-speaking adults aged 18 to 85 who are competent to give consent scheduled for primary AVF formation at either the radial or brachial artery. Exclusion criteria are allergy to local anaesthetic, coagulopathy, infection at the anaesthetic or surgical site, patient preference for general or alternative anaesthesia, significant peripheral neuropathy or neurologic disorder affecting the upper extremity, pregnancy, previous AVF creation on the ipsilateral arm, known cephalic vein occlusion, central vein stenosis, brachial or radial artery stenosis and vein or artery less than 1.8 mm, as measured by ultrasound.

## Consent

The process of consent will be in accordance with the Declaration of Helsinki. All suitable patients will be fully informed that they are being asked to participate in a research study. The procedures involved in the study, and the chances of being assigned randomly to one of two groups, will be explained in person and via an information sheet approved by the West of Scotland Ethics Committee. A signed consent form will be obtained from each patient and retained by the investigators. Patients will be made aware of their right to withdraw from the study at any time without adverse effects on their clinical care.

### Pre-operative management

At room temperature, in a supine position and without any flexing of the elbow, the internal diameter of the cephalic vein in all patients will be measured by a blinded observer using a linear ultrasound probe at the wrist and elbow. The internal diameter of the basilic vein at the elbow will also be measured. In all cases, minimal compression will be applied with the probe and the vein measured in its most circular shape. To reduce intra-observer variability, the average of three measurements will be recorded for each parameter. Each vein measurement position will be marked on the skin. Flow through the radial artery or brachial artery, depending on which is being used for the AVF, will also be measured using Doppler ultrasound. In order to calculate flow, both vessel cross sectional area and time averaged velocity need to be measured. Cross sectional area is calculated by the machine after using ultrasound to measure vessel diameter. Time averaged velocity is measured in the long access with Doppler ultrasound maintaining an angle of insonation of less than 60 degrees. Using these figures, flow can then be calculated [19]. Again, the point of measurement will be marked on the skin and an average of three measurements will be recorded to reduce intra-observer variability.

